## Abstract

**Background:**

Central nervous system tumours constitute 25% of all childhood cancers; more than half are located in the posterior fossa and surgery is usually part of therapy. One of the most disabling late effects of posterior fossa tumour surgery is the cerebellar mutism syndrome (CMS) which has been reported in up to 39% of the patients but the exact incidence is uncertain since milder cases may be unrecognized. Recovery is usually incomplete. Reported risk factors are tumour type, midline location and brainstem involvement, but the exact aetiology, surgical and other risk factors, the clinical course and strategies for prevention and treatment are yet to be determined.

**Methods:**

This observational, prospective, multicentre study will include 500 children with posterior fossa tumours. It opened late 2014 with participation from 20 Nordic and Baltic centres. From 2016, five British centres and four Dutch centres will join with a total annual accrual of 130 patients. Three other major European centres are invited to join from 2016/17. Follow-up will run for 12 months after inclusion of the last patient. All patients are treated according to local practice. Clinical data are collected through standardized online registration at pre-determined time points pre- and postoperatively. Neurological status and speech functions are examined pre-operatively and postoperatively at 1–4 weeks, 2 and 12 months. Pre- and postoperative speech samples are recorded and analysed. Imaging will be reviewed centrally. Pathology is classified according to the 2007 WHO system. Germline DNA will be collected from all patients for associations between CMS characteristics and host genome variants including pathway profiles.

**Discussion:**

Through prospective and detailed collection of information on 1) differences in incidence and clinical course of CMS for different patient and tumour characteristics, 2) standardized surgical data and their association with CMS, 3) diversities and results of other therapeutic interventions, and 4) the role of host genome variants, we aim to achieve a better understanding of risk factors for and the clinical course of CMS - with the ultimate goal of defining strategies for prevention and treatment of this severely disabling condition.

**Trial registration:**

Clinicaltrials.gov: NCT02300766, date of registration: November 21, 2014.

## Background

### Incidence and definition of CMS

Central nervous system (CNS) tumours account for 25% of all cancers in children and over half of these are located in the posterior fossa [1]. For most of these patients, treatment includes surgery. Posterior fossa tumours in children are associated with high risk of chronic neurological and neurocognitive disability [2–6]. The cerebellar mutism syndrome (CMS) refers to the constellation of transient mutism, ataxia, hypotonia and irritability following surgery for cerebellar or fourth ventricle tumours in children and adolescents [7]. Although some patients may recover completely, recovery may be prolonged, and many are left with permanent disabling sequelae in the form of e.g. dysarthria, dysfluency, slowed speech rate and ataxia. Many may in addition be burdened by emotional problems and lower IQ [8–12].

The spectrum of CMS definitions varies greatly [7, 12–14], leading to differences in reported incidence and uncertainties about recovery. Incidence figures thus range from 8% [15, 16] to 32% [17] in children with any kind of cerebellar tumour when a variety of definitions are used, compared to 24% [12] to 39% [18] in patients with medulloblastomas using a more precise CMS definition. A recent study of 148 children with cerebellar tumours found that the overall incidence of the broader Posterior Fossa Syndrome was 28%, subdivided by tumour pathology into 40% for medulloblastoma, 16% for astrocytoma and 20% for ependymoma [19]. The CMS definition created by the Neurology Committee of the Children’s Cancer Group in USA in 1993 is currently the only one associated with a specific scoring scale [12] and is used in this project.

### Risk factors and prevention

Cerebellar mutism is thought to be caused by bilateral disturbance of the dentate nuclei and/or their efferents [16, 20–24]. Ataxia and irritability together with other cognitive, affective and motor symptoms that are frequently observed in CMS patients are caused by damage to various parts of the cerebellum and cerebello-cerebral pathways passing through the brainstem [25–28]. This can result in secondary diaschisis of supratentorial brain areas due to lack of excitatory input from cerebellum [29–31].

*Known risk factors* are brainstem involvement by the tumour, midline location and tumour type; thus the incidence in children with medulloblastoma is two to three times higher than for astrocytoma or ependymoma but the biological mechanisms behind these associations are uncertain [12, 19, 22, 32–35]. Recently *proposed risk factors* include brainstem compression by the tumour, pre-operative language impairment, low socioeconomic level of the families and left-handedness [24, 36–38]; however, these remain to be verified on large patient cohorts. Tumour size, neurosurgical techniques and approaches, radical resection and younger age at diagnosis are *uncertain risk factors*, as previous studies have been inconclusive [12, 23, 32–35, 39, 40]. Gender, hydrocephalus, post-operative central nervous system infections, type of neurosurgeon (adult/paediatric), and oedema/swelling of the cerebellum have not been significantly correlated to CMS and are considered *unlikely risk factors* [12, 16, 34, 35, 41, 42].

In traumatic brain injury common host genomic variants are related to the severity of symptoms and degree of recovery [43–45]. Similar associations are likely for surgical brain injury, but such studies have not been performed for CMS.

### Non-surgical treatment

Supportive speech and rehabilitation therapy is often offered to patients with CMS, but the benefit hereof has not been demonstrated. No publications exist on systematic approaches to pharmacological neuroprotection, and pharmacological interventions are only sporadically reported in the literature [46–50]. Glucocorticosteroids are routinely given to most patients pre-, intra- and post-operatively to reduce inflammation and edema [51] [52], but there is no consensus recommendation and the impact on the clinical course of CMS is undetermined.

### Aims

The study focuses on the risk factors for development and severity of CMS including surgery (approaches, techniques and tissue and vascular damage, re-operation) and host genome variants. The aims of this study are thus to describe differences in incidence, severity and clinical course of CMS related to:Clinical factors: gender, age, handedness, speech, language and neuropsychological abilities before and after surgery.Tumour factors: histological tumour type and tumour locationSurgical factors: Surgical strategy and surgical trauma including access routes, removal technique, tissue and vascular injury, bleeding and primary surgery vs. re-operationNon-surgical interventions: glucocorticosteroids, other symptomatic medication and chemo- and radiotherapyHost genome variants

## Methods/design

### Design

This open observational study is registered at Clinicaltrials.gov (file NCT02300766) and EANS (http://www.sbns.org.uk/index.php/research/eu-multi-centre-trials). All children younger than 18 years with a tumour in the posterior fossa requiring surgery or open biopsy at one of the participating centres will be included following informed consent. Patients who have received surgery, chemotherapy and/or radiotherapy previously are also eligible. The study will run for five years with a targeted sample size of 500 patients. It opened late 2014 with participation from 20 Nordic and Baltic centres. From 2016, five British centres and four Dutch centres will join leading to an expected annual accrual of 130 patients. Three other major European centres are invited to join from 2016/17. The target of 500 patients is expected to be reached in 2018. Patients will be followed for 12 months after inclusion of the last patient, and the study will thus be completed during 2019.The participating centres provide surgery and supportive care according to local practice and register all study information in an online database developed specifically for this study. Consensus concerning the study aims, study design and data registration was achieved at three international planning meetings among the initiating centres during 2013. The annual enrolment from each country will be compared to the number of registered patients in the national cancer registries to document the inclusion rate and representativeness.

### Primary endpoint

The primary endpoint is incidence and severity of CMS. Symptoms and severity are scored according to the CMS survey published by Robertsons et al. [12]. Our main focus is the impact of different surgical tumour approaches. We hypothesize that 1) minimally traumatic techniques and 2) sparing the dentate nuclei and their efferents will be associated with a 50% reduced risk of CMS when compared to more invasive tumour removal approaches. Furthermore, we hypothesize that the risk of developing CMS is higher after re-operation(s) compared to primary surgery.

### Secondary endpoint

The secondary endpoint is incidence of “reduced speech output” defined as “severely reduced speech production limited to single words or short sentences which can only be elicited after vigorous stimulation” [19]. The risk of reduced speech output will be related to different surgical approaches with the underlying hypothesis that damage to the dentate nuclei and/or their efferents increases the risk.

Furthermore, we want to explore the following:

#### Genetics

We will analyse the role of host genome variants on development, severity and recovery from CMS by carrying out broad genetic pathway profiling of all study participants using both non-CMS cases from the study cohort and non-CNS tumour patients as controls. Genotyping will use single nucleotide polymorphism (SNP) exome enriched arrays (e.g. Illumina Omni2.5-exome platform). We will apply agnostic genome-wide association studies (GWAS) as well as more complex pathway analyses. Thus, we will interrogate combined effects of multiple SNPs acting in the same pathways or protein-protein interaction complexes using our validated non-linear machine learning algorithm (artificial neural networks approach) [53, 54], which allows testing of a large range of pathways from various databases. This approach will yield hypotheses easier to test across cohorts and also provide mechanistic insights. We hypothesize that host genome variants explain at least 50% of the variation in incidence of CMS and at least 40% of the variation in severity, duration and level of recovery from the CMS.

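### Non-CNS tumour patients are named as controls for the CMS genetics without a separate role, so tumour-susceptibility variants can be read as CMS variants

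*Protocol article*

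**What the plan says.** The Genetics section sets three outcomes: "We will analyse the role of host genome variants on development, severity and recovery from CMS". The comparison groups are given in the same sentence: "using both non-CMS cases from the study cohort and non-CNS tumour patients as controls". The methods are broad: "We will apply agnostic genome-wide association studies (GWAS) as well as more complex pathway analyses". The section does not say which control group is primary, whether the two are pooled, what the external group is for, or whether a signal found against it must also appear inside the cohort.

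Two other parts of the article bear on this choice.

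- Incidence and definition of CMS describes the syndrome as arising "following surgery for cerebellar or fourth ventricle tumours in children and adolescents". Eligibility under Design matches this: "All children younger than 18 years with a tumour in the posterior fossa requiring surgery or open biopsy".
- Risk factors and prevention states that "the incidence in children with medulloblastoma is two to three times higher than for astrocytoma or ependymoma". The Background cites a series of 148 children in which the broader Posterior Fossa Syndrome occurred in 28% overall, "subdivided by tumour pathology into 40% for medulloblastoma, 16% for astrocytoma and 20% for ependymoma".

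**The concern.** A control for a genetic study of CMS should be someone who could have developed CMS and did not. On the article's own definition, a patient with a non-CNS tumour could not. CMS status is undefined for such a patient, and so are severity and recovery, two of the three outcomes.

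CMS cases differ from non-CNS tumour patients in two ways: they have a posterior fossa tumour, and they developed CMS after its removal. A contrast between the groups cannot tell these apart. Because CMS is more frequent after medulloblastoma surgery, the mixture leans towards medulloblastoma susceptibility. Variants for the controls' own cancers can also appear, with the sign reversed.

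This is bias from the choice of comparison group. A stricter significance threshold makes a false declaration rarer but does not move the estimate back to the null. At stake is whether a reported host variant says anything about who develops CMS after surgery.

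**Working it through.** **The plan's own genetic figure.** Statistical considerations gives 343 patients for an overall CMS risk of 20%, a SNP frequency of 30%, a doubled risk, a 5% level and 90% power. With risks of 32% in carriers and 16% in non-carriers, k = 0.7/0.3 non-carriers per carrier and a mean risk of 0.3 × 0.32 + 0.7 × 0.16 = 0.208, the two-sided pooled-variance formula is

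n = [1.96 √((1 + 1/k) × 0.208 × 0.792) + 1.2816 √(0.32 × 0.68 + 0.16 × 0.84/k)]² / (0.32 − 0.16)² = 102.9, rounded up to 103 carriers.

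The total is 103/0.30 = 343, which reproduces the stated figure. (Risks solved for exactly 20% overall, 30.8% and 15.4%, give 363; power at 343 is then 88.5%.) The figure compares carriers with non-carriers inside the operated cohort. It uses no external controls.

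**Illustration 1: a medulloblastoma variant with no effect on CMS.**

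Inputs from the article: risks of 40% (medulloblastoma) and 16% (astrocytoma, here applied to all other tumours). These are rates for the broader Posterior Fossa Syndrome, not for CMS as this study defines it.

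Assumptions not in the article: medulloblastoma share 40%; 30% carriers among other posterior fossa patients and among non-CNS controls; odds ratio for medulloblastoma 1.5 or 2.0.

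- Overall risk: 0.4 × 0.40 + 0.6 × 0.16 = 0.256.
- Medulloblastoma share of CMS cases: 0.160/0.256 = 62.5%.
- Medulloblastoma share of non-CMS patients: 0.4 × 0.60/0.744 = 32.3%.
- Medulloblastoma share of non-CNS controls: 0%.
- Carriers in medulloblastoma: odds = OR × 0.30/0.70, giving 39.1% (OR 1.5) and 46.2% (OR 2.0).

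Carrier frequency in each group is share × carriers in medulloblastoma + (1 − share) × 0.30:

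| Variant OR for medulloblastoma | CMS cases | Non-CMS | Non-CNS | Spurious OR, external | Spurious OR, internal, histology ignored |
|---|---|---|---|---|---|
| 1.5 | 35.7% | 33.0% | 30.0% | 1.30 | 1.13 |
| 2.0 | 40.1% | 35.2% | 30.0% | 1.56 | 1.23 |

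Pooling the two control groups gives a carrier frequency between the non-CMS and non-CNS columns, so the spurious odds ratio then lies between the last two columns.

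**Range.** With the medulloblastoma share at 30% to 50% and the risk in other tumours at 16% to 20%, the spurious odds ratio runs from 1.21 to 1.66 externally and from 1.09 to 1.23 internally.

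**Illustration 2: a variant for posterior fossa tumours in general, with no effect on CMS.** Within the cohort, CMS and non-CMS patients carry it equally often, so the internal odds ratio is 1 and false rejection stays at 5%. Against non-CNS controls the odds ratio is the full susceptibility effect. With 100 CMS cases (20% of 500) and an assumed 1000 external controls with 30% carriers, a two-sided 5% test rejects 47% of the time for an odds ratio of 1.5 and 90% for 2.0. For 100 to 5000 external controls, the figure for 2.0 runs from 66% to 92%. At an assumed genome-wide threshold of 5e-8 it is at most about 3%.

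**What stratification can do.** Within a histology stratum, cases and internal controls have the same carrier frequency in Illustration 1, so the internal bias disappears. No histology stratum contains both CMS cases and non-CNS tumour patients, so stratifying cannot repair the external contrast.

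**The case against.** The strongest reply is that the same sentence already names the right controls, the non-CMS patients of the cohort. Nothing says that the external group is primary, that the groups are pooled, or that a signal against the external group alone would be called a CMS variant. Using that group as a check on tumour susceptibility would fit the present wording. A reader might infer that tumour-susceptibility variants will be reported as CMS variants. The article does not support that; it supports only that they can be.

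The reply also notes that a journal article commonly leaves covariates, ancestry adjustment and the order of contrasts to a fuller document. That stands: silence on histology adjustment is no fault here, and the internal figures above only show why the adjustment belongs in the fix. The choice of control group is different, because the article states it.

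Three further limits stand. The variant odds ratios and the medulloblastoma share are assumed. At a genome-wide threshold, single-variant false positives of this kind would be rare, although the article fixes no threshold for the genome-wide analysis, and its pathway methods combine many variants. Finally, the genetic work is listed among matters to explore, and the surgical primary endpoint does not depend on it. The article also does not say that the non-CNS tumour patients are children, so no argument should rest on their age.

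**Conclusion.** The concern holds in a limited form. The article names a control group that was never at risk of CMS, for outcomes that this group cannot have, and does not separate its role from that of the valid internal controls. Used alone or pooled, it can make tumour-susceptibility variants look like CMS variants.

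Under the stated assumptions the distortion is an odds ratio of 1.30 to 1.56 (range 1.21 to 1.66) where the true CMS effect is nil. The internal contrast without histology gives 1.13 to 1.23 (range 1.09 to 1.23). These sizes are illustrative: they rest on assumed variant effects and tumour mix, and on risks for a broader syndrome than the study's CMS. That the external contrast mixes the two kinds of susceptibility does not depend on them.

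The stronger reading, that the genetic analysis as a whole is invalid, is not supported, because the within-cohort comparison is already planned. Importance is moderate.

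**What to change.** State in the Genetics section that CMS versus non-CMS patients within the cohort is the primary genetic contrast for development of CMS, stratified by or adjusted for tumour histology. State that severity and recovery are analysed among CMS patients only. Give the non-CNS tumour patients one role: to flag signals that reflect tumour susceptibility. They should not serve as CMS controls, either pooled or alone.

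The cost is a change of wording and fewer controls. At the article's 20% overall risk, 0.80/0.20 = 4 non-CMS patients remain per case; under the main illustration, 0.744/0.256 = 2.9. At the highest risk in the range examined (50% medulloblastoma, 20% in other tumours, 30% overall) it is 0.70/0.30 = 2.3. The 343-patient calculation stays as it is.

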#### Other non-surgical treatments including glucocorticosteroids

The possible effects of chemo- and radiotherapy on recovery from CMS will be investigated. We hypothesize that chemo- and radiotherapy delay recovery from CMS. For descriptive documentation purposes we also ask for information on medications given specifically to treat the symptoms of CMS.

We hypothesize that glucocorticosteroids 1) given preoperatively protect against CMS due to reduced oedema; 2) given intraoperatively increase the risk of CMS due to worsening of acute neurological injury by hyperglycaemia; 3) given postoperatively negatively affect the course of CMS as earlier studies have shown a negative effect of glucocorticosteroids on the outcome of traumatic brain injury [55, 56]. It may be expected that most patients receive glucocorticosteroids at all 3 time points which would make it difficult to assess added positive and negative effect in the same patients.

#### Tumour type

The incidence of the CMS will be correlated to tumour histology using the 2007 WHO classification. We hypothesize that the risk of CMS is highest among patients with medulloblastoma. With increasing focus on subtyping of medulloblastoma [57] this additional classification may later be added to the risk factor analysis.

#### Neuroradiology

Tumour location, enhancement pattern, invasiveness and growth velocity may affect the risk and severity of CMS [12, 18, 58]. Accordingly, we hypothesize that a statistical risk of CMS may be predicted by defining specific neuroradiological features [59–61]. Likewise, postoperative neuroradiological features could give prognostic information about probable degree of recovery.

#### Handedness

We will determine whether the risk of the CMS varies according to handedness. We hypothesize that the risk of CMS is increased in left-handed patients, and possibly even more so in patients with medulloblastoma [24].

#### Language and speech

Our hypothesis that preoperative speech and language impairment increases the risk of postoperative speech and language deficits will be explored by recording pre- and postoperative speech (e.g. articulation, prosodic features and voice) and language (e.g. word finding difficulties, fluency and narrative ability) statuses and relating these to incidence and course of CMS. All speech recordings will be analysed nationally by speech therapists.

### Registration of data

The following data will be registered at five time points by online standard registration forms:

#### 1. Preoperatively

Hospital, country, patient related variables such as date of birth, handedness, comorbidities, bilingualism, gender and date of diagnosis, medical history and preoperative neurological status. A speech and language test will be performed and recorded. If the patient is younger than two years a bedside assessment of speech will be performed instead of a formalized test. A two millilitre blood sample for genetic analysis will be collected.

#### 2. Postoperatively within 72 h of surgery

Surgery related variables such as date, patient position during surgery, surgical approach, tumour removal method (én bloc, piecemeal or ultrasonic aspiration), duration and course of operation, damage to non-tumour tissue, complications, technology employed (endoscopy, neuronavigation, electrophysiological monitoring etc.), surgeon’s estimate of tumour resection extent and presence of preoperative hydrocephalus.

#### 3. Postoperatively within one to four weeks from surgery

Approximately one to two weeks post-operatively: neurological examination, postoperative speech and language status including speech and language recording or bedside assessment and medications used for treatment of CMS.

Approximately four weeks post-operatively: Development and treatment of postoperative intracranial haematoma and hydrocephalus, leakage of cerebrospinal fluid and need for ventilator. These complications are usually seen earlier but we wait until the fourth post-operative week to register these in order to ensure no complications are missed.

